#### Abstinence from week 9–24

Defined as the proportion of subjects who maintained abstinence between weeks 9 to 24, inclusive, measured by subject self-report of smoking consumption on a weekly basis, confirmed by exhaled CO.

#### Abstinence from week 9–24, week 9–52 and 37–52 in high AB responders

Defined as biochemically confirmed 16-week abstinence at 6 months (week 9–24), 44-week abstinence at 12 months (week 9–52) and 16-week abstinence at 12 months (week 37–52) among the high antibody responders.

#### Lapse and relapse rate from week 12–52

Among participants with 4-week abstinence status at 12 weeks, we define relapse as at least 2 consecutive weekly self-reports that are positive for tobacco use. A lapse is defined as 1 weekly self-report for tobacco use followed and preceded by 1 weekly self-report for tobacco abstinence.

#### Withdrawal symptoms

Withdrawal symptoms will be measured 14 times by using the MNWS (item scores 0=“none” to 4=“severe”), reflecting craving for cigarettes, anger, irritability, frustration, anxiety, nervousness, depression, difficulty concentrating, insomnia, restlessness, and increased appetite or weight gain [24]. The MNWS will be collected at screening, weeks 12–15, weeks 26–29, and weeks 49–52.

#### Nicotine dependency

Nicotine dependency will be measured by the FTND and is administered at screening, week −2, 24, and week 52 as long as the participant continues to smoke [25].

#### Cigarette consumption

Information on cigarette consumption will be collected based on the participants’ self-reports on smoking status, in which they record their total cigarette consumption for the prior week.

### Data analysis

#### Data and Safety Monitoring Board (DSMB)

An independent DSMB will review all safety data available at pre-determined time points to decide on the continuation of the trial regarding the safety profile of the investigational product. We will use SPSS^®^ version 16.0 or higher to perform all statistical analyses.

#### Efficacy analysis

For our primary analysis we will compare NicVAX^®^ versus placebo, both co-administered with varenicline, in an intention-to-treat (ITT) analysis using a using a logistic regression model with corresponding 95% confidence interval, and p-value. The study has a single primary variable, and as such, no adjustments for multiple comparisons will be made. All statistical tests will be two-sided tests performed at a 0.050 level of significance.

#### Efficacy analysis in high AB responders

Subjects who receive NicVAX will be stratified based on peak antibody concentration (Cmax) and based on area under the curve. For each stratification scheme (AUC or Cmax) subjects will be placed into two or more percentile groups (50^th^, 33^rd^, 25^th^) based on AUC or Cmax. For each stratification method, the abstinence rate in the top antibody group compared with placebo will be initially performed first for the top 25^th^ percentile group. If the initial test is positive, the hypothesis will be retested for subsequent percentile groups (i.e., 33^rd^, 50^th^). The role of anti-nicotine antibodies will be established if the abstinent rate for the high responders (e.g. either 50^th^, 33^rd^, 25^th^ percentile) groups is superior to placebo.

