### Nicotine vaccination: immunogenicity

Immunogenicity has been shown to be dose-related. Additional injections and higher vaccine doses have been shown to be related to stronger immune responses and higher antibody titers [18]. These antibody titers typically peak following the final injection when 4 or 5 vaccinations are administered [16].The peak geometric mean antibody concentration reported in response to the nicotine conjugate vaccine NicVAX^®^ was 45 μg/ml in the subgroup who received 5 injections with 400 μg of NicVAX^®^[16]. Previous data reported no difference in antibody response between smokers and non-smokers [19].

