## Methods/design

### Study design

In this phase IIb trial a total of 600 participants will be randomized in a 1:1 ratio to one of the 2 treatment groups, receiving either 400 μg NicVAX^®^ or matching placebo, both combined with open-label varenicline and intensive counseling (see Figure 1). After a 2-week screening period, in which the participant will be medically approved, the follow-up for each participant is 54 weeks. All participants will receive open-label varenicline starting at week 0 until week 12, together with a total of 6 injections in weeks −2, 2, 6, 10, 14, and 24. The target quit date will be set 1 week after starting the use of varenicline (3 weeks after randomization). Several quit re-challenges, where continuing smokers plan a new quit date, will be implemented at week 12, 16, and 26 for all participants who are not able to quit smoking successfully, corresponding to predicted elevations of anti-nicotine Ab levels occurring 2 weeks after the 4^th^, 5^th^, and 6^th^ vaccinations.

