### Sample size calculation

The primary end point of this study is biochemically validated prolonged abstinence from week 9 to week 52. The effect of a 12-week varenicline treatment on abstinence from smoking during 12 months has been shown to be about 22% [11,21]. A sample size of 300 smokers per group would provide 90% power to detect a difference in abstinence between the intervention and control groups of at least 12% (22% in the placebo group vs. 34% in the NicVAX^®^ group) with a 5% Type I error rate. As a consequence of the imputation analysis, where participants who become lost to follow-up will be included in the analysis as a smoker according to current practice in this field of research, the sample size is not corrected for lost to follow-up [22].

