### Handling drop outs and missing data

Participants who withdraw from the study will be considered smokers for the remainder of the study. In the absence of CO measurement during a planned clinical visit, the confirmation on smoking status will be imputed using the CO measurements of both bordering visits. An abstinent status will only be assigned when both bordering visits are no more than one planned clinical visit apart and both CO measurements at these visits are < 10 ppm (i.e., participants are not allowed to miss two consecutive visits with CO measurements). In all other cases, a smoking status will be assigned. The refusal by a participant to undergo CO testing during a clinic visit will be considered to be an elevated CO level and the participant to be a smoker.

Any missing self-reports on smoking status will be imputed using both of the bordering non-missing weekly self reports. A missing self-report will be assigned an abstinent status only when both bordering self-reports have abstinent status. This imputation will only be carried out if the two bordering self-reports are no more than 4 weeks apart.

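### The high-antibody analysis sets a vaccine subgroup likely to be depleted of dropouts against the whole placebo arm, so superiority there cannot establish a role for antibodies

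*Protocol article*

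**What the plan says.** All references are to the protocol article.

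- **Efficacy analysis in high AB responders.** The grouping is defined as follows: "Subjects who receive NicVAX will be stratified based on peak antibody concentration (Cmax) and based on area under the curve". Under both schemes the top 25% is tested against placebo first; the 33% and 50% groups follow only if that test is positive. No restriction on the placebo arm is given. The decision rule reads: "The role of anti-nicotine antibodies will be established if the abstinent rate for the high responders", in any of the three percentile groups, is superior to placebo.
- **Handling drop outs and missing data.** "Participants who withdraw from the study will be considered smokers for the remainder of the study".
- **Nicotine vaccination: immunogenicity.** More injections give higher titres, and "These antibody titers typically peak following the final injection when 4 or 5 vaccinations are administered".
- **Study design, Immunogenicity and Table 1.** Injections are given at weeks −2, 2, 6, 10, 14 and 24. Antibody is sampled at 13 time points from week −2 to week 52, including weeks 12 and 14.
- **Secondary objectives, item 4.** The responder analysis covers three abstinence windows: weeks 9–52, 9–24 and 37–52.
- **Efficacy analysis.** "All statistical tests will be two-sided tests performed at a 0.050 level of significance". There is one primary variable and no adjustment for multiple comparisons.

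**The concern.** Responder status is known only after randomisation and only in one arm, so randomisation does not protect this comparison. Retention feeds both sides of it unequally. A vaccinated participant who leaves early misses later injections and samples, tends to have a low AUC or Cmax, and so tends to fall outside the top group; that participant is also scored a smoker. A placebo participant who leaves early is scored a smoker too, but stays in the comparator. The top group gains from staying in the trial even if antibodies do nothing.

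The rule then draws a causal conclusion from the result. The article reports that two phase III trials missed their primary endpoint, so if the primary analysis here is also null, a positive result in this subgroup could carry the interpretation.

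**Working it through.** **1. The plan's own figure.** "600 participants will be randomized in a 1:1 ratio to one of the 2 treatment groups"; "A sample size of 300 smokers per group would provide 90% power to detect a difference in abstinence", with "22% in the placebo group vs. 34% in the NicVAX^®^ group) with a 5% Type I error rate". Two-sided 5%, 90% power:

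n = [1.960·√(2·0.28·0.72) + 1.282·√(0.22·0.78 + 0.34·0.66)]² / 0.12² = 292.1, so 293 per arm. At 300 per arm the power is 90.7%. The stated figure reproduces, so 300 per arm and 22% abstinence serve as the base.

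**2. Null set-up.** The vaccine raises antibody but has no effect on smoking. Both arms have 22% abstinence and the same withdrawal proportion d. The top quarter is 75 of 300, tested against all 300 placebo. A two-sided 5% test declares the vaccine superior by chance in 2.5% of trials. The article gives no d, so d is an assumption.

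**3. Apparent abstinence in the top group.** Withdrawals count as smokers, so abstinence among those who stay is 0.22/(1−d). If a share s of the top group has withdrawn, its rate is

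p = 0.22·(1−s)/(1−d).

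With s = d there is no bias. With s < d the top group looks better than placebo.

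**4. Chance of a false declaration of superiority.** Φ{[(p − 0.22) − 1.96·SE₀]/SE₁}, where SE₀ uses the pooled rate and SE₁ the separate rates, with 75 and 300 participants.

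In a null simulation using AUC to last visit and an assumed antibody profile, the top quarter held about 5/10/15% dropouts when 15/25/35% of the arm withdrew. Putting these into the formulas:

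| d | s | p | Excess over 22% | False superiority |
|---|---|---|---|---|
| 15% | 5% | 0.22·0.95/0.85 = 24.6% | +2.6 points | 7% |
| 25% | 10% | 0.22·0.90/0.75 = 26.4% | +4.4 points | 13% |
| 35% | 15% | 0.22·0.85/0.65 = 28.8% | +6.8 points | 25% |

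Worked line for d = 25%: pooled rate 0.2288, SE₀ = 0.0542, SE₁ = 0.0562, and (0.044 − 1.96·0.0542)/0.0562 = −1.11, giving 13%.

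**5. Dependence on the antibody summary.** Null simulation, weeks 9–52, top quarter, nominal 2.5%:

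| Assumed withdrawal | AUC to last visit | Time-averaged AUC | Cmax |
|---|---|---|---|
| 15% | 7% | 5% | 3% |
| 25% | 13% | 7% | 6% |
| 35% | 27% | 11% | 8% |

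The first column agrees with step 4. If dropout is unrelated to antibody, the rate is about 3% whatever the withdrawal.

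**6. Does matching on retention remove it?** With responder status fixed at week 14 and both arms restricted to participants still attending at week 14, false superiority was 2–3%. This simulation made antibody independent of quitting, so it shows that the retention bias goes, not that all confounding does.

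**The case against.** **The top group is not shown to be dropout-free.** A reader might infer that it contains no withdrawals. Nothing in the article excludes them from the ranking, and a late leaver can still have a high Cmax. A dropout-free group at 25% withdrawal would show 0.22/0.75 = 29.3%, an excess of 7.3 points, against about 4.4 in step 4. Only depletion is supported. This objection stands in full.

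**The AUC window is not given.** A condensed article can leave the derivation of AUC and Cmax to the full protocol or analysis plan. That is fair, and it is why three versions are shown. It also means the article does not settle whether samples taken after week 24 could decide responder status for the week 9–24 outcome. It does not rescue the comparison: unrestricted placebo and the conclusion to be drawn are both stated.

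**Multiplicity.** A reader might infer that success in any of two schemes and three windows suffices, and that the error rate is badly inflated as a result. The article does not say that any one window is enough, the percentile steps are ordered, and one primary variable is declared. Without withdrawal, any of the six tests passes in about 5% of null trials, against 2.5% for one. This is a secondary matter.

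**The Discussion's argument.** A reader might think that it rests on this subgroup. It rests on the top 30% responders of earlier trials.

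**Antibody response is reported as similar in smokers and non-smokers.** That weakens one route of confounding but does not touch selection by retention.

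**This is a secondary analysis in a phase IIb trial.** True; it lowers the severity.

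**Conclusion.** The concern holds. The stated comparison favours the vaccine whenever withdrawal lowers measured antibody, and it cannot by itself establish that antibodies work. Instead of 2.5%, false superiority may run from about 3–8% (Cmax) to about 7–27% (AUC to last visit) over an assumed withdrawal range of 15–35%. Those figures rest on equal withdrawal in both arms, 22% abstinence in each and an assumed antibody profile. The direction rests only on the stated rules and on the expectation that early leavers reach lower antibody levels.

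A reader might infer that the trial's main efficacy result is compromised. It is not: the primary intention-to-treat comparison uses all randomised participants in both arms. The point is one that should be fixed, not one on which the trial stands or falls.

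**What to change.** 1. In the section on high AB responders, replace *will be established* with *will be explored as supportive evidence*.
2. Make a landmark comparison the lead version. Define responders by antibody concentration at one pre-specified visit already sampled, such as week 14, and compare them with placebo participants still in follow-up at that visit. State how withdrawals enter AUC and Cmax if those versions are kept as secondary.
3. Support it with a logistic model within the vaccine arm: abstinence on log antibody at the landmark, adjusted for baseline FTND and center.
4. Name one scheme and one abstinence window as the lead. Weeks 9–52 matches the primary outcome; weeks 37–52 lies wholly after a week-14 landmark.

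**Cost.** Wording and programming only; no new data. The claim becomes weaker. Table 1 places the week-14 sample at the fifth-injection visit, so the responder definition reflects only the first four of six injections. Week 14 also falls inside the week 9–24 and 9–52 windows. Responders are still compared with unselected placebo, so confounding by host factors or adherence remains; this is why the softer wording is needed as well.

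### The high-responder rule controls error within one antibody metric and one abstinence window, but two metrics and up to three windows can each win the claim at an unadjusted 0.05

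*Protocol article*

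**What the plan says.** Under Efficacy analysis, the article sets one level for everything: "All statistical tests will be two-sided tests performed at a 0.050 level of significance". It also declines any adjustment, with its reason: "The study has a single primary variable, and as such, no adjustments for multiple comparisons will be made".

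Under Efficacy analysis in high AB responders:

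- Two metrics are used, with no priority between them: "Subjects who receive NicVAX will be stratified based on peak antibody concentration (Cmax) and based on area under the curve".
- Three cuts are foreseen: "subjects will be placed into two or more percentile groups (50^th^, 33^rd^, 25^th^) based on AUC or Cmax".
- For each metric the top 25% is compared with placebo first. Then: "If the initial test is positive, the hypothesis will be retested for subsequent percentile groups".
- The antibody role counts as established if the abstinence rate for the "high responders (e.g. either 50^th^, 33^rd^, 25^th^ percentile) groups is superior to placebo".

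That section names no abstinence window. Secondary objectives (item 4) and the outcome definition for high responders give three windows (weeks 9–24, 9–52 and 37–52), all to be assessed "among the high antibody responders". Appendix A gives two for the same subset (weeks 9–52 and 37–52).

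**The concern.** A fixed sequence of tests keeps the error rate at the level of its first test, but only along one sequence. Here the sequence is started once per metric and, on the main-text list, once per window: 2 × 3 = 6 entry tests, any of which can deliver the claim. The reason given for not adjusting, a single primary variable, protects the primary comparison. It does not reach a second, separately worded claim that has its own success rule.

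The claim carries weight. The article reports that two phase III trials of the vaccine missed their primary endpoint, and its Discussion rests much of the remaining case on high antibody responders doing better. If the primary result here is also negative, the antibody statement is the one most likely to be carried forward.

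**Working it through.** **Reproducing the plan's own figure.** Inputs from Sample size calculation: 300 per group, 22% v 34%, two-sided 5%.

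- Pooled rate 0.28. Standard error under the null: √(2 × 0.28 × 0.72 / 300) = 0.0367.
- Standard error under the alternative: √((0.22 × 0.78 + 0.34 × 0.66) / 300) = 0.0363.
- z = (0.12 − 1.96 × 0.0367) / 0.0363 ≈ 1.32, so power is about 0.907.

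The stated 90% is reproduced with a two-sided test. The article gives no error rate for the antibody claim, so that has to be worked out.

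**Group sizes.** The top 25%, 33% and 50% of 300 vaccinees are 75, 100 and 150, each compared with 300 on placebo.

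**Nominal rate.** A two-sided 0.05 test carries 0.025 in the direction of superiority, which is the direction the rule requires.

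**What the gate does.** Under the global null, a false result at 33% or 50% can arise only after a false result at 25%. With the gate obeyed, the cuts therefore add no error. The number that matters is the number of entry tests: metrics × windows.

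**Bound if entry tests were independent**, 1 − 0.975^k:

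- k = 2: 4.9%
- k = 4: 9.6%
- k = 6: 14.1%

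The tests are in fact strongly correlated, since they share the placebo group, have overlapping top groups and nested windows. Simulation is needed for a realistic figure.

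**Simulation under no effect.** 20,000–30,000 trials per setting, 300 per arm, antibody level unrelated to abstinence, pooled two-proportion z test. Assumptions not in the documents:

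- Cmax–AUC correlation 0.5 to 0.95.
- Abstinence 32–35% for weeks 9–24 and 30–35% for weeks 37–52.
- The article's 22% is used for weeks 9–52, which is nested in both other windows.

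| Reading of the rule | False superiority claim (nominal 2.5%) | Significant in either direction (nominal 5%) |
|---|---|---|
| One metric, one window, gate obeyed | 2.7–3.0% | about 5% |
| Two metrics, one window, gate obeyed | 4–5% | 7–9% |
| Two metrics, two windows (Appendix A), gate obeyed | 6–7% | 11–13% |
| Two metrics, three windows (main text), gate obeyed | 8–10% | 15–19% |
| Any of 2 × 3 × 3 = 18 tests, gate ignored | 12–15% | 23–30% |

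Relative to 2.5%, the gated rows with two metrics are about 1.5–2 times nominal for one window, 2.3–2.8 times for two and 3–4 times for three. The ungated row is about 5–6 times.

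**Check of the repairs.** One metric, one window and a strict sequence is the first row of the table. If all six entry tests stay, testing each at 0.05/6 = 0.0083 gives 1.7–2.2% for superiority and 2.9–3.6% in either direction. Splitting 0.025 to each metric gives at most 2 × 0.0125 = 2.5% for superiority, but only if one window is named.

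**The case against.** The strongest reply is that this is a secondary objective in a phase IIb trial, that the article openly says it does not adjust, and that the order of metrics and windows may be fixed in a statistical analysis plan that is not shown. Much of this is fair: the primary test is untouched, and silence on ordering would not by itself be a fault in a condensed article. But the article is not silent. It gives a decision rule with cuts, order, level and a confirmatory conclusion, and that rule as written does not hold its level.

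A second reply is that the high-responder analysis section speaks of the abstinence rate in the singular, so perhaps one window decides. That is possible, and it is why the one-window figure is shown. It lowers the excess without removing it, because two metrics remain.

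Three stronger readings are tempting, and the documents do not support them:

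- *That* either *contradicts the step-down and opens 18 routes to the claim.* If the gate is obeyed, no 33% or 50% result exists without a positive 25% result, and *either* is simply redundant. It conflicts only when read apart from the sentences before it. The wording is ambiguous and should be reconciled, but the 12–15% figure belongs to that isolated reading alone.
- *That the claim has no error control at all.* The step-down does control error within one metric and one window. What is missing is control across them.
- *That dropout pushes the rates much higher still.* The article gives no dropout rate and does not say how dropouts are ranked on antibody level. Any such bias is a different matter from multiplicity, and naming one metric and one window would not remove it.

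**Conclusion.** The concern holds in this form: the claim about antibodies is worded as confirmatory, can be won through two metrics and one to three windows, and is not covered by the single-primary-variable argument. The false superiority rate is above nominal on every reading of the published text, from about 4–5% if one window decides to about 8–10% on the three windows in the main text. These ranges depend on the assumed Cmax–AUC correlation, the assumed rates in the shorter windows, and a simple two-proportion test standing in for whatever model is used. To describe the error as several times nominal is right for three windows, and too strong if one window decides. This is a repair worth making to a secondary claim; the validity of the primary analysis is not in question.

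**What to change.** In Efficacy analysis in high AB responders:

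1. Name one metric (Cmax or AUC) and one window, for example weeks 9–52 to match the primary outcome, as deciding the antibody claim.
2. State that the top 25% must be significant before the top 33% is tested, and the 33% before the 50%, stopping at the first non-significant result. The present text makes the larger groups conditional on the 25% test but does not say that the 50% waits for the 33%.
3. Reword *either* so that it follows this order.
4. Label the other metric and windows as exploratory, and bring the window lists in Secondary objectives and Appendix A into agreement.

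If the sponsor prefers to keep more than one route, alpha should be split over all entry tests that are kept: 0.025 per metric is enough only if one window is also named, and 0.05/6 applies if all six stay.

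The change is to wording only, with no effect on sample size, data collection or the primary test. The cost is fewer routes to a positive antibody statement or, with split alpha, less power on each.
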